### Review descriptions

2.7

These will be the review descriptions: physical capacity (VO_2_ peak at the cardiopulmonary exercise test, CPET); hemodynamic responses during the CPET; vascular function (HR and PA, flow-mediated dilatation, FMD); autonomic (heart rate and blood pressure variability); sympathovagal balance; and baroreflex control at rest.

### Interventions

2.8

The LLLT group will receive the laser application at 8 points, twice a week, over a 2-month period, totaling 16 sessions. Each point will be stimulated for 8 seconds in the soft palate, uvula, pharyngeal walls, palatine tonsils, and on the tongue base (to the extent that the anatomy and compliance will allow). See Figure 2.

**Figure 2 F2:**
[figure not shown]
The 8 points of LLLT application: soft palate, uvula, pharyngeal walls, palatine tonsils, and on the tongue base. The LASER therapy will apply twice a week, over a 2-month period, totaling 16 sessions. Each point will be stimulated for 8 seconds in the soft palate, uvula, pharyngeal walls, palatine tonsils, and on the tongue base. Figure adapted from Storchi IF.^[4]^ LASER = light amplification by stimulated emission of radiation, LLLT = low-level laser therapy.

The laser used will be the Therapy Plus NS 13678 (Mark DMC, São Paulo, Brazil), with a spot diameter of 2.35 mm and a spot area of 0.0434 cm^2^. For that, the wavelength will be 808 nm (nanometers), with a power of 250 mW (milliwatts), and an energy of 2 J (joules). The LLLT application data is best specified in Table 1.

**Table 1 T1:**
[figure not shown]
LLLT protocol applied by continuous infrared in patients with obstructive sleep apnea.

In the C group, they will receive placebo applications of the photobiomodulation, with only the use of a guiding light that is visually very similar to the LLLT, for the same 8 seconds and at the same 8 points, but without any effects, because the laser will be turned off.

During the ensuing routines, the patients will undergo 2 months of treatment and they will receive 16 sessions of photobiomodulation (2 times a week).

During the sessions, the researchers will remind the participants of the importance of adherence to the treatment sessions, in order to improve their compliance with the intervention protocol. The participants will be instructed to continue their usual routines for health conditions as usual.

### Study variables

2.9

The primary variable of this study will be the AHI per hour of sleep. The secondary variables will be improvements in the autonomic and hemodynamic control of the subjects with OSA.

#### Berlin questionnaire

2.9.1

The OSA screening will be conducted when using the Berlin Questionnaire (BQ). The patients with a high risk of OSA will be submitted to polysomnography. Before the evaluations of PSG, all of the patients will complete the 11-item self-reporting BQ (divided into 3 categories), with the aim of detecting important symptoms for the diagnosis of OSA. Those subjects that indicate in at least 2 positive categories will be considered at a high risk for OSA. In Category 1, a positive score will be defined as persistent symptoms (3–4 times/wk) in ≥2 questions about their snoring. In Category 2, a positive score will be defined as persistent (3–4 times/wk) for wake-time sleepiness, drowsy when driving, or both. In Category 3, a positive score will be defined as a history of high blood pressure or a body mass index (BMI) ≥30 kg/m^2^.^[7–9]^

#### Polysomnography

2.9.2

There will be overnight polysomnography. The researchers will evaluate OSA by an overnight PSG (Night One Philips Respironics Digital System, 4 Channels, Philips Respironics, Philips Medical Devices) as previously described.^[5]^ The device is also equipped with software, in order to measure the relevant parameters of the PSG. The PSG will start at around 10:00 pm and will finish at around 6:00 am. The AHI will be calculated as the total number of respiratory events (apneas plus hypopneas), divided by the total sleep time, and expressed in events per hour (events/h). The AHI cutoff for OSA will be based on the Task Force of the American Academy of Sleep Medicine.^[5]^ The severity of OSA will be classified as such: non-OSA for AHI <5 events/h, mild OSA for AHI from 5 to 14.9 events/h, moderate OSA for AHI from 15 to 29.9 events/h, and severe OSA for AHI will be ≥30 events/h.^[5]^ Apnea will be defined as a 90% decrease of airflow for at least 10 seconds, while hypopnea will be defined by a >50% decline in airflow in respiratory signals for at least 10 seconds, accompanied by 3% oxygen desaturation.^[5]^ All of the equipment to be used is appropriate for the legal regulations of Brazil and the equipment will use standardized positioning, in order to minimize any experimental bias.

#### Qualitative variables

2.9.3

Anatomy of the oral cavity (Modified Mallampati Test)^[10]^Daytime sleepiness (Epworth Scale)^[11]^Quality of life (SF 36; Medical Outcome Study)^[12]^Stress level (the Brazilian version of the Perceived Stress Scale)^[13]^;Level of physical activity (International Physical Activity Questionnaire [IPAQ])^[14]^.

#### Epworth sleepiness scale

2.9.4

The Epworth sleepiness scale (ESS) is a questionnaire to detect daytime sleepiness, consisting of a simple subjective scale, and covering 8 different daytime situations. The subjects will be asked to rate on a scale of 0 (those who would never doze) to 3 (high chances of dozing); how likely they would be to doze off or fall asleep in 8 situations, based on their recent everyday life. A distinction will be made between dozing off and simply feeling tired. Thus, the scale will be ranged from 0 to 24, and excessive daytime sleepiness will be defined when the score is ≥11.^[11,15]^

The questionnaire will take a full 10 minutes to be completed. The data that is to be collected for this study will only be administered by the principal investigators (the authors of this document).

### Statistical analysis and data analysis plan

2.10

All of the personal records of the participants, such as the signed ICF, will be stored in locked file cabinets. The information will be transferred to a computer by [name] (the author of this protocol) and the participants will be identified by ID numbers. All of this collected data will be stored on a university computer, protected by a password, and accessed by [name] (a co-author of this protocol) for the statistical analysis, or by the other researchers supervising this study. The Shapiro-Wilk test will be used to test the normality of the data. If the data are nonparametric, the normalization will be performed by a mathematical strategy. The Shapiro-Wilk test will be performed in order to analyze the normality of the distribution between the groups, and thus use the appropriate inferences tests. The descriptive data will be presented in relative frequency, with measures of a central tendency and dispersion, according to the nature of the variables, by a mean ± standard error, or by a median and interquartile interval.

Assuming the normality of the data, the characteristics of the groups at the pre-intervention time will be compared by the Student *t* test for the independent samples. For the analysis of the effects of the laser applications, a comparison of the means through the analysis of variance (ANOVA) for repeated measurements will be performed, associated with the post-hoc test when the effect is verified. Where necessary, nonparametric equivalent tests shall be used. The ANOVA test for the independent variables, followed by Bonferroni post-hoc test, will be used for the inferential analysis. A *P* < .05 value will be considered statistically significant.

The analyses will be performed in the Statistic Package for the Social Science—IBM SPSS Statistics for Windows, Version 20.0 (IBM Corp, Armonk, NY). for all of the calculations, being adopted to a level of significance of 5%.

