### Study design

2.1

This will be a clinical, randomized, comparative, and blind study. There will be 36 patients randomized into 2 treatment groups: LLLT treatment or placebo (C) (Fig. 1). The study will be implemented over 2 months, divided into 16 sessions, 2 times a week. It will be conducted at the Medicine Outpatient Clinic of the Nove de Julho University, in the city of São Paulo, Brazil. This protocol was written and was based on the Standard Protocol Items: Recommendations for Interventional Trials (SPIRIT). The dissemination and the registration for participation in the study will be carried out through the Nove de Julho University website. The participants will be residents who will mainly be recruited from the city of São Paulo. The participants will be informed about the research, the procedures, the risks, and the benefits by [name] (the author of this protocol). If they agree, they will sign the informed consent form (ICF). Only the participants, who after reading and agreeing to the protocol, and who sign the ICF, will be part of the study.

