### Inclusion criteria

2.3

This study will be conducted on men and women aged 30 to 60 years, who are at a risk of OSA, by screening with the Berlin questionnaire. Those patients who have agreed to participate in the study will perform nocturnal polysomnography. Those diagnosed with moderate and severe OSA (apnea/hypopnea index, AHI ≥15 events/h) will be invited to participate in the study.

Subsequently, they will be submitted to clinical/physical examinations, with measurements of demographic and body composition (bioimpedance), as well as with blood pressure and blood tests. The blood samples will be collected from the venous blood after 12 hours of overnight fasting, in order to determine the total serum cholesterol, the triglycerides, the high-density lipoprotein (HDL) cholesterol (enzymatic method), and the plasma glucose (standard glucose oxidase method) concentrations.

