### Sample size calculation

2.5

The sample size was calculated at http://www.openepi.com. It was determined according to an earlier study, with a similar population, displaying metabolic syndrome, and sleep apnea.^[6]^ The primary outcome was a reduction of the AHI. A power of 80% was considered, with a bicaudal type 1 error of 0.05, in order to detect a difference in the AHI of 16 events/h, assuming a standard deviation of 20 events/h.

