### Randomization

2.6

Through the website http://www.randomization.com/, a random block list was generated for the 2 studied groups, LLLT and C. The randomization plan was for 9 blocks of 4 individuals. For both of the groups, the order of the randomization will occur at the entrance to the protocol, by consulting the random list and indicating to which group the patient should be allocated.

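### The analysis of the primary outcome, AHI, hangs on a Shapiro-Wilk test with two unnamed, unordered fallbacks; one baseline-adjusted between-arm analysis should be fixed instead

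*Protocol article*

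**What the plan says.** The primary outcome is AHI: "The primary variable of this study will be the AHI per hour of sleep" (protocol article, section 2.9). Entry is selected on that same variable: "Those diagnosed with moderate and severe OSA (apnea/hypopnea index, AHI ≥15 events/h) will be invited to participate in the study" (section 2.3), with no upper limit.

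Section 2.10 sets out the analysis for all variables together:
- Shapiro-Wilk is applied to the data, and its result determines which inferential tests follow.
- If normality fails: "If the data are nonparametric, the normalization will be performed by a mathematical strategy".
- In a later paragraph: "Where necessary, nonparametric equivalent tests shall be used".
- The default for the laser effect is repeated-measures ANOVA with a post-hoc test. A further sentence names an ANOVA for independent variables with Bonferroni correction, without saying which variables it covers.

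The section does not say whether normality is judged on baseline, post-treatment values, change or residuals, and it sets no rule of its own for AHI.

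**The concern.** A plan should fix the primary test before anyone sees outcome data. Here the text makes the test conditional on the data and then leaves a second choice open once the condition fails. A t test on transformed change and a rank test on raw change address different hypotheses and can disagree in a trial this small. If the analyst may choose between them with both results in view, the 5% level no longer holds exactly.

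There is also a gap in what the fallback tests. With two groups and two visits, the group-by-time term of the repeated-measures ANOVA is the comparison of mean change between arms. The rank procedures commonly put in its place (Wilcoxon signed-rank, Friedman, Mann-Whitney at one visit) contain no such term. A within-arm test does not compare laser with sham, and patients selected for a high baseline AHI tend to fall on re-measurement in both arms.

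This is more than detail left for a separate analysis plan. The article states a decision rule, and the rule itself is open-ended.

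**Working it through.** **Inputs.** 36 patients in total: "There will be 36 patients randomized into 2 treatment groups" (section 2.1). Allocation: "The randomization plan was for 9 blocks of 4 individuals" (section 2.6), so 18 per arm if blocks are balanced. "A power of 80% was considered, with a bicaudal type 1 error of 0.05"; "detect a difference in the AHI of 16 events/h, assuming a standard deviation of 20 events/h" (both section 2.5). The article gives no information on the shape of the AHI distribution or on the correlation between baseline and post-treatment AHI. Both are assumptions below.

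**1. The plan's own figure.** n per arm = 2 × (1.960 + 0.842)² × (20/16)² = 2 × 7.85 × 1.5625 = 24.5, so 25 per arm and 50 in total. The stated 36 is not reproduced. That is a separate matter and is not relied on here. At 18 per arm, SE = 20 × √(2/18) = 6.67, 16/6.67 = 2.40, and power = Φ(2.40 − 1.96) = 67%.

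**2. How often would Shapiro-Wilk reject?** Simulated baseline AHI bounded at 15, SD about 20 to 23, 3,000 trials per shape, test at 5%:

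| Assumed shape | One arm, n=18 | Either arm | Pooled, n=36 |
|---|---|---|---|
| 15 + exponential | 79% | 96% | 99% |
| Truncated lognormal (two versions) | 54-71% | 78-91% | 89-97% |
| 15 + gamma, shape 1.5 or 2 | 49-60% | 74-84% | 84-92% |
| 15 + gamma, shape 4 | 28% | 47% | 53% |
| Truncated normal (three versions) | 6-27% | 11-45% | 11-60% |

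For change in AHI over the same shapes (pooled, n=36), rejection is 4-6% if within-person variation is additive (SD 12) and 46-60% if it is proportional (log-SD 0.35). The answer therefore depends on the shape assumed and on which quantity is tested.

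**3. Type I error with 18 per arm and no effect.** Shapes and within-person variation are assumed throughout.
- Shapiro-Wilk gate with one fallback fixed in advance: 3.8-5.2%.
- Smaller P of the log-scale and rank analyses: 5.6-6.6% after a failed gate under the exponential and gamma shapes, and 5.5-7% under truncated lognormal AHI (source mean 25-30, SD 20, log-scale correlation 0.6-0.8).
- Adding Mann-Whitney on post-treatment AHI as a third option under the same lognormal model: about 10%.

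**4. What baseline adjustment gives.** Take SD 20 at each visit and correlation r.
- Unadjusted group-by-time: SD of change = 20√(2(1 − r)).
- ANCOVA: residual SD = 20√(1 − r²).
- Variance ratio, ANCOVA to change = (1 − r²)/(2(1 − r)) = (1 + r)/2, which never exceeds 1.

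At r = 0.5 the SD of change is 20.0, SE 6.67 and power Φ(2.40 − 1.96) = 67%. The ANCOVA SD is 17.32, SE 17.32 × √(2/18) = 5.77, and power Φ(2.77 − 1.96) = 79%.

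| r (assumed) | Group-by-time | ANCOVA |
|---|---|---|
| 0.3 | 53% | 71% |
| 0.5 | 67% | 79% |
| 0.7 | 87% | 92% |

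These are normal approximations; t-based values are slightly lower.

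**The case against.** Several stronger readings are tempting, and the document does not support them.

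- **That AHI cut off at 15 is almost certain to fail the test.** The article says nothing about the shape of AHI, and rejection runs from 11% to 99% with the shape assumed. The cut-off also binds only baseline AHI, not post-treatment AHI or change, which carry the treatment effect.
- **That the two fallbacks contradict each other.** Transforming first and using rank tests only if that fails is a coherent reading. Section 2.10 also covers ordinal scores such as Mallampati, for which rank tests are natural. What is missing is the order and the trigger.
- **That the gate destroys the 5% level.** A gate with one fixed fallback holds about 5%. The excess comes from the open choice, and with two options it is one or two percentage points.
- **That the fallback will be separate within-arm tests.** The Discussion states that laser is compared with placebo, and Mann-Whitney on change would be a valid rank comparison of the arms. The text permits a within-arm substitute but does not prescribe one.
- **That a log-scale model is clearly more powerful.** Data simulated as lognormal with a proportional effect favour a log model by construction. The gain shown above comes from baseline adjustment alone.

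One may also say that naming a transformation or rank test belongs in a statistical analysis plan. That is fair for the names alone. It does not cover a published rule that makes the primary test depend on the data and leaves two routes open.

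**Conclusion.** The point holds in a limited form. Section 2.10 leaves the primary AHI test to be settled after the data are seen, through a normality gate followed by two unspecified and unordered fallbacks, and it does not guarantee that the fallback compares the arms. Use of a fallback is plausible because entry is bounded below and open above, but its probability cannot be derived from the article. The inflation of type I error is modest: about 5.5-7% for a choice between two P values, under the assumed shapes.

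The practical gain from correction is a fixed primary test and the use of baseline AHI already collected, worth about 12 points of power at an assumed correlation of 0.5 (18 points at 0.3, 5 at 0.7). This should be corrected, but it is not a fatal flaw.

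**What to change.** Remove the Shapiro-Wilk gate for AHI and fix one between-arm primary analysis before unblinding: ANCOVA of post-treatment AHI on arm and baseline AHI, reporting the adjusted difference with its 95% confidence interval.

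Fix the scale at the same time. Events/h matches the basis of the sample size in section 2.5 and is the simpler choice. If the log scale is preferred, state the exact transformation and how an AHI of zero is handled, and report the events/h difference beside the ratio. If a constant is added before taking logs, the result is not a ratio of geometric means of AHI itself.

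Name one sensitivity analysis: the same model on the other scale, or a rank-based between-arm comparison of change. Keep the existing fallback wording for secondary variables only.

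The cost is a change of wording, with no new data or patients. ANCOVA uses one degree of freedom for the baseline term, which is minor with 36 patients. If the log scale is chosen, the primary effect becomes a ratio and is one step removed from the planned 16 events/h.

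### Section 2.10 names the standard error as the dispersion measure that accompanies the mean; for descriptive data it should be the standard deviation

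*Protocol article*

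**What the plan says.** Section 2.10 (Statistical analysis and data analysis plan) first states the purpose of the summaries: "The descriptive data will be presented in relative frequency, with measures of a central tendency and dispersion". The choice among them depends on the nature of each variable. It then names the two forms for quantitative data: "by a mean ± standard error, or by a median and interquartile interval".

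Read as a whole, the sentence pairs the mean with the standard error and the median with the interquartile interval. The standard deviation is not named as a descriptive statistic anywhere in the article. It appears once, in Section 2.5 (Sample size calculation), as a planning assumption: the trial is sized "in order to detect a difference in the AHI of 16 events/h, assuming a standard deviation of 20 events/h".

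**The concern.** The two forms answer different questions. An interquartile interval describes how patients differ from one another. A standard error describes the uncertainty of an estimated mean, and gets smaller with every patient added even if the patients are no more alike. Offering it as dispersion puts the wrong quantity under the stated purpose.

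What is at stake is the description of the patients. Eligibility starts at an AHI of 15 events/h with no stated upper limit, so moderate and severe disease are mixed and the spread at baseline is part of knowing who was studied. A small ± figure understates that heterogeneity for anyone who takes it as what the plan calls it. Because the form depends on the variable, one table could also carry both kinds of figure side by side, with spreads that cannot be compared by eye.

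**Working it through.** **Inputs**

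- Total sample: 36 patients in two groups (Section 2.1).
- Allocation list: "The randomization plan was for 9 blocks of 4 individuals" (Section 2.6). Check: 9 × 4 = 36, which agrees with Section 2.1.
- Allocation ratio: not stated in words. Assuming 1:1, n = 36/2 = 18 per arm.
- Standard deviation (SD) of AHI: 20 events/h (Section 2.5). The article does not say whether this refers to a single measurement or to a change, so it serves here only as an illustration of scale.

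**Step 1: ratio of the two quantities.** SE = SD/√n, so SD/SE = √n. With n = 18, √18 = 4.24. The ratio depends on n alone, so it is the same for every variable summarised by arm as a mean with no missing values.

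**Step 2: the planning figure.** SE = 20/√18 = 4.71. A spread of 20 events/h would be printed as ±4.7.

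**Step 3: comparison with the other form.** For a normal variable the interquartile width is 2 × 0.6745 × SD = 2 × 0.6745 × 20 ≈ 27 events/h. The same data would therefore be described by ±4.7 under one form and by an interval about 27 wide under the other.

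**Step 4: sensitivity to n per arm.** The losses below are assumptions; the article gives none.

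| Patients per arm | SD/SE = √n | SE if SD = 20 |
|---|---|---|
| 14 | 3.74 | 5.35 |
| 16 | 4.00 | 5.00 |
| 17 | 4.12 | 4.85 |
| 18 (as planned) | 4.24 | 4.71 |
| 25 | 5.00 | 4.00 |

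The last row is there because the inputs of Section 2.5 (two-sided 5%, power 80%, difference 16, SD 20) give 2 × [20 × (1.960 + 0.842)/16]² = 24.5, hence 25 per arm and 50 in total, not 36. That discrepancy is a separate matter. Here it only shows that the ratio stays at roughly four to five whichever size is used.

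**The case against.** The best defence is that a figure labelled as a standard error is a correct standard error. The plan names it openly and nowhere says it will be printed without a label. If n is given, any reader recovers the standard deviation as SE × √n, for example 4.71 × 4.24 = 20. No inference depends on it: the t test, the repeated-measures ANOVA and the P values are computed from the data, and the sample size already uses a standard deviation. All of this stands, and it keeps the point minor. It does not remove it, because the plan itself files the standard error under dispersion and so invites the misreading.

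Three stronger readings are tempting but not supported:

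- A reader might infer that every reported spread will be about four times too small. The same sentence offers the median with interquartile interval, which is a valid measure of spread, and frequencies carry no standard error.
- A reader might infer an 18-fold error in the size of a later trial, since sample size goes with the square of the standard deviation. That factor is simply n per arm (4.24² = 18), would arise in any trial of this size, and needs someone to mistake a labelled standard error for a standard deviation. It is not a measure of harm in this plan.
- A reader might object that no confidence interval is promised for the between-arm difference, or ask for one from an adjusted model. An article may leave intervals to the full protocol or analysis plan, and Section 2.10 describes no adjusted model.

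**Conclusion.** The point holds in a narrow form. Section 2.10 states a rule that gives the wrong quantity for its own stated purpose. This is something the article says, not something left for another document to supply. For variables summarised by arm as a mean, the printed ± figure would be about 4.2 times smaller than the standard deviation: ±4.7 in place of 20 events/h at the planning value.

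The size rests on 18 per arm, with 1:1 allocation inferred from 36 patients and nine blocks of four, and on complete data; with 14 to 17 analysed per arm the ratio would be 3.7 to 4.1. The consequence is confined to descriptive reporting, and the severity is low.

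**What to change.** In the descriptive-data sentence of Section 2.10, replace mean ± standard error with mean ± standard deviation, and leave the median with interquartile interval and the relative frequencies as they are. Keep the standard error, or a confidence interval, for estimated means and differences only, labelled as such.

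The cost is one sentence, changed before results are tabulated. Conduct, data collection, tests and sample size are untouched. Any amendment would follow the route the article already describes, through the ethics committee and the registry.

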**Figure 1 F1:**
[figure not shown]
Flowchart of the study.

The study will start in March 2020. The study is not yet recruiting. After the recruitment, the researchers will check if the patients meet the inclusion/exclusion criteria based upon the anamnesis, the Berlin questionnaire, and the polysomnography evaluation.

The patients and/or the public will not be involved in the design, the recruitment, or the conduct of the study. The participants will be men and women who are sedentary, who are not on a diet or drug therapies, and who are at a risk of OSA, by screening with the Berlin questionnaire. Initially, they will perform nocturnal polysomnography. Those diagnosed with moderate and severe OSA (apnea/hypopnea index, AHI ≥15 events/h) will be invited to participate in the study.

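### The planned repeated-measures ANOVA does not name its deciding term or adjust for baseline AHI; a single baseline-adjusted comparison of the arms would be clearer and more precise at no cost

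*Protocol article*

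**What the plan says.** Protocol article, section 2.10, assesses the effects of the laser by a "comparison of the means through the analysis of variance (ANOVA) for repeated measurements will be performed, associated with the post-hoc test", with the post-hoc step following once an effect is found. It adds: "The ANOVA test for the independent variables, followed by Bonferroni post-hoc test, will be used for the inferential analysis". The baseline groups are compared by t test, but baseline AHI does not enter the outcome analysis. The same section provides for transformation of non-normal data and for nonparametric equivalents.

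AHI is the primary variable (section 2.9), and section 2.5 puts it this way: "The primary outcome was a reduction of the AHI". Section 3 has the measurements taken before and after the 16 sessions. Section 2.1 states the entry rule: "Those diagnosed with moderate and severe OSA (apnea/hypopnea index, AHI ≥15 events/h) will be invited to participate in the study". No other pre-treatment polysomnography is described.

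**The concern.** Two arms and two visits give three F tests: time, group and group-by-time. Only group-by-time compares the arms on change. The text does not say which of them decides. Each factor has two levels, so post-hoc tests can only compare individual arm-by-visit means, including pre against post within the laser arm.

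Two things are at stake. The first is clarity. Patients enter on a high AHI reading, so some fall may occur in both arms without any treatment effect. A time effect or a fall within the laser arm could then be read as efficacy, although neither is a randomised comparison. The second is precision. The term that does compare the arms fairly discards information that adjustment for baseline would use.

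**Working it through.** **Inputs.** Section 2.5 gives the error rates, "A power of 80% was considered, with a bicaudal type 1 error of 0.05", and the effect, "in order to detect a difference in the AHI of 16 events/h, assuming a standard deviation of 20 events/h". Section 2.1 gives 36 patients. Section 2.6 says "The randomization plan was for 9 blocks of 4 individuals" for two groups, taken here as 18 per arm. The pre-post correlation r is not given, so 0.3 to 0.8 is assumed. Equal SDs at both visits and no dropout are also assumed. Section 2.5 does not say whether SD 20 belongs to one reading or to the change, so both are shown.

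**1. The plan's own figure.** n per arm = 2 × 20² × (1.960 + 0.842)² / 16² = 24.5, so 25 per arm and 50 in total (26 per arm by the t distribution). The stated 36 does not reproduce. At 18 per arm the standard error is 20 × √(2/18) = 6.67 and the noncentrality is 16/6.67 = 2.40. Power is 64.5% by the noncentral t (67% by the normal approximation). The sample size is a separate matter; here it only shows that there is little power to spare.

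**2. SD 20 as the SD of one reading.** The group-by-time test has SD 20 × √(2(1 − r)) on 34 df. ANCOVA has residual SD 20 × √(1 − r²) on 33 df. The ratio of the variances is 2/(1 + r). At r = 0.5:
- Group-by-time: SD 20.00, noncentrality 2.40, power 64.5%.
- ANCOVA: SD 20 × √0.75 = 17.32, standard error 5.77, noncentrality 2.77, power 76.7%.

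| r | SD, group-by-time | Power | SD, ANCOVA | Power | Variance ratio |
|---|---|---|---|---|---|
| 0.3 | 23.66 | 50.4% | 19.08 | 68.5% | 1.54 |
| 0.5 | 20.00 | 64.5% | 17.32 | 76.7% | 1.33 |
| 0.6 | 17.89 | 74.1% | 16.00 | 82.9% | 1.25 |
| 0.7 | 15.49 | 85.3% | 14.28 | 90.3% | 1.18 |
| 0.8 | 12.65 | 95.8% | 12.00 | 97.3% | 1.11 |

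**3. SD 20 as the SD of change.** Group-by-time power is then 64.5% whatever r is. The single-reading variance is 20²/(2(1 − r)), so the ANCOVA SD is 20 × √((1 + r)/2).

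| r | SD, ANCOVA | Power, ANCOVA |
|---|---|---|
| 0.3 | 16.12 | 82.4% |
| 0.5 | 17.32 | 76.7% |
| 0.6 | 17.89 | 74.0% |
| 0.7 | 18.44 | 71.5% |
| 0.8 | 18.97 | 69.0% |

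**4. What the unnamed term could let through.** This was simulated with no laser effect: 18 per arm, SD 20, 20,000 trials per setting. With no fall in either arm, every test rejects in about 5% of trials. With an assumed equal fall of 5 events/h in both arms, at r = 0.3/0.5/0.7:
- Group-by-time stays at about 5%.
- The time effect is significant in 23/31/47%.
- The laser arm's own pre-post test is significant in 14/17/25%.

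The fall of 5 is an illustration and does not come from the documents. A second simulation drew AHI from an assumed lognormal source (mean 20–35, SD 18–22, night-to-night correlation 0.6–0.8 on the log scale) with entry at 15 or more. It gave falls of 0.4 to 4.1 events/h, with the time effect significant in 5% to 23% of trials. The lower end is the nominal rate.

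**The case against.** Three objections carry weight.

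- **The intended term can be inferred.** The introduction says that the groups will be compared, and the discussion rests the evaluation on laser against placebo. Group-by-time is therefore the natural reading, and an article may leave such detail to an analysis plan. A reader might infer that the plan will credit a pre-post fall to the laser. The documents do not support that: nowhere do they say that a time effect or a within-arm test decides efficacy. What remains is an ambiguity in the stated method that is easily closed.
- **Group-by-time is valid.** A reader might infer that the planned ANOVA is wrong. It is not: its group-by-time term is a randomised comparison with the correct error rate. The case for ANCOVA is efficiency. If SD 20 is that of one reading, the gain is about 5 points at r = 0.7 and under 2 at r = 0.8.
- **The second ANOVA cannot be pinned down.** It is tempting to call it an unpaired test that ignores the repeated measures. Its wording names neither factor nor visit and may refer only to the ANOVA factors, so that charge fails. Bonferroni on a two-level factor is redundant but harmless.

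The objections do not remove the efficiency point. The article itself fixes a method without baseline adjustment, and baseline AHI is already measured.

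**Conclusion.** The point holds as a free improvement, not as an error that invalidates the trial. The planned between-arm term is valid but less precise than ANCOVA at every correlation below 1. At 18 per arm the gain is about 18 percentage points at r = 0.3, 12 at 0.5, 9 at 0.6, 5 at 0.7 and 1.5 at 0.8 if SD 20 is that of one reading. It runs from about 18 points at r = 0.3 to 4.5 at r = 0.8 if SD 20 is that of change. These sizes rest on an assumed correlation, equal SDs at both visits and no dropout.

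ANCOVA should not be taken to rescue the sample size. Under the single-reading assumption it reaches 80% power only from r of about 0.56. Under the SD-of-change assumption it has already dropped to 76.7% at r = 0.5.

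The risk that a non-randomised contrast is read as efficacy is real but cannot be sized from the documents, because the shared fall is unknown.

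**What to change.** In section 2.10:

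- Name one primary test: ANCOVA of post-treatment AHI on arm, with baseline AHI as covariate. Report the adjusted between-arm difference, its 95% CI and one two-sided P value.
- Prespecify the scale so that the model fits the section's own transformation provision, for example log AHI at both visits if residuals are skewed, with the effect then reported as a ratio. Say what role the nonparametric alternative keeps, for example as a sensitivity analysis.
- State that the time effect and within-arm pre-post results are descriptive and support no efficacy claim.
- Clarify what the second ANOVA with Bonferroni tests, or drop it. With two arms there is nothing to correct.

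The cost is analysis wording only: baseline AHI is already collected and the named software fits the model. The change should be made before anyone sees unblinded outcome data.
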